##### Measures to assess multi-modal synchrony

Synchrony will be measured based on four modalities (Table 1).

**Table 1 Tab1:** The 28 candidate markers of synchrony from 4 modalities

Dimensions	Features to be used	Details	Data acquisition	Data quantification
Physiological	Heart rate variability (GSR +) [70]	HRV may indicate mental and biological functioning. [70] EDA is a measure of the activity of the sympathetic nervous system, which is related to a state of increased arousal [71]. Their potential importance in measuring synchrony has been demonstrated [24, 72, 73]	Shimmer 3	Python EDA analysis [72]
	Electrodermal activity[71]			
Motional	Two predefined motion regions of interest (ROIs): (a) head region (b) gesture and body region [33, 74]	Motion energy is defined as the difference in pixel values between consecutive video frames. The detection of frame-by-frame changes enables quantification of the changes in predefined ROIs. Its potential importance in measuring synchrony has been demonstrated [6, 16]	Video	Motion energy analysis [75]
	Cross-correlation analysis of amplitude and quality of movement across multiple body segments		Video; AR51 motion capture; Unreal engine (Epic Games, Inc.)	
Acoustic	Fundamental frequency, speech rate, pause, jitter	Vocal acoustics was found to convey information regarding the arousal [76, 77] and the emotional [78–80] and interpersonal [81, 82] characteristics of individuals Its potential importance in measuring synchrony has been demonstrated. [83, 84]	Audio	Praat software package [85]
Facial expressions	20 Action units that interact to generate different facial expressions. [86]	AFFDEX classifier identifies basic emotions using a combination of 20 anatomically-based facial actions. Its potential importance in measuring synchrony has been demonstrated. [30, 87]	Audio	iMotions Biometric Research Platform, open face

**Interaction with virtual humans.** Interactions with virtual humans will take place in a VR environment in the same room in which participants met their human listeners. The participant will wear an immersive VR headset and will be part of a virtual environment designed to mimic a real room. Participants will view their own movements mirrored in the virtual environment and hear the real voice of the listener (a stranger). However, the listener’s movements in the virtual environment will not reflect their actual movements but rather pre-recorded gestures will be used to manipulate the synchrony between the virtual human listener and the participant, either by hyperactivating or deactivating it. To do so, we will create a “bank” of listening gestures based on previous listening data during dyadic interactions. The 3D movements of the participant will be recorded, characterized, and used in real time to manipulate the movements of the virtual human listener. Specifically, hyperactivation of the synchrony system will be operationalized by triggering gestures that will be time- and amplitude-locked to the participant’s movements, and deactivation of the system will be operationalized by triggering gestures not synchronized to those of the participant.

In the VR environment, a head-mounted display (HMD) (Meta Quest 3) will provide a computer-generated image of the virtual room, similar in all aspects (size, furniture, etc.) to the actual one in which the participants interacted with the other human figures. A markerless motion capture system (AR51) will provide full-body movement kinematic data in the virtual environment, allowing the participant to be represented by a first-person perspective virtual body whose virtual movements reflect the real body movements of the participant in real time. The result is a sensorimotor congruence (because of visual and proprioceptive alignment) that creates an illusion of ownership and agency of the participants over their virtual bodies. After participants are engaged in dyadic interactions with multiple other humans, they will enter the virtual reality lab and will be fitted with a Meta Quest 3 HMD. They will be familiarized with their virtual bodies seen from a first-person perspective and seated on a real chair, conforming to a virtual chair. Shortly thereafter, a virtual human listener will enter the room.^2^

#### The VR environment

The Meta Quest 3 has a nominal field of view of 110°, with a resolution of 2,064 × 2,208px per eye displayed at 72 Hz. The experiment will take place in the same room where all interactions with humans will occur. The virtual environment will be implemented using the Unreal engine (Epic Games, Inc.). Participants’ virtual body skeletons will be rendered using a proprietary SDK by AR51 from Unreal. One male and one female virtual human character will be selected from an existing bank and will be used for all male and female participants. Approximate character age will be selected to fall within the normal range of the sample population of participants, and their looks will be casual.

#### Overview of statistical analyses

For each participant in interaction with each interacting-other, we will collect 28 features from the four types of modalities. We will compute the autoregressive (“counting on the self”) and interactive (“counting on the other”) effects for each of the 28 features of the participant with each of the 28 features of the interacting other to assess cross-modality interactions. Similarly to previous research from our lab, we will calculate the autoregressive and interactive effects using a series of Actor-Partner Interdependence Models (APIM[88]), which estimate cross-lagged associations between the participant and each interacting partner, measuring within-session synchrony. We will use the autoregressive (actor) effect, also referred to as *intra*personal effect, to estimate “counting on the self,” which will serve to describe the deactivation pattern. We will use the interactive (partner) effect, referred to as *inter*personal effect, to estimate “counting on the other,” which will serve to describe the hyperactivation pattern [89]. Data will be detrended before analysis. To calculate actor and partner effects for each individual, we will include random effects on the participant and interacting-other actor and partner effects and intercept. We will extract these random effects for each participant and interacting-other in each dyad using empirical Bayes residuals.

##### Identifying the individual-specific trait-like signature

We will blend all autoregressive and interactive effects of all possible pairs of the 28 features of the participant and the 28 features of the interacting-other to explore whether clusters of single individuals emerge from the observations. We will use Support Vector Machine (SVMs) to conduct two types of classification tasks: participant and relationship. Our lab has expertise in using SVMs to identify patterns in high-resolution data [90]. This method is based on the relatively straightforward idea that, given two classes of data graphed onto a two-dimensional space based on some identifiable features, a theoretically infinite number of lines can be drawn to divide the data. SVM has been used to identify the best dividing line as one that is maximally distant from the nearest data point of each class, providing the largest possible buffer space between the two classes. This buffer space defines the optimal separating hyperplane (OSH). The OSH separates the classes of data and minimizes the risk that new data will be incorrectly classified [91]. SVM is not limited to two- or even three-dimensional space, nor to linearly-separable classes. Using the SVM, we will be able to explore whether homogenous individual-specific signatures incorporating all the interactions of a given individual will emerge and whether they will be different from all the interactions in which the given individual did not take part (i.e., which will form the other individuals’ signatures).

##### Identifying individual differences in the individual-specific signature

To explore the existence of the proposed three patterns of individual differences, we will use the most differentiating features of autoregressive and interactive effects, as found in the SVM analyses described above. We will use the autoregressive (actor) effect to estimate the deactivation pattern and the interactive (partner) effect to estimate the hyperactivation pattern. To explore whether the participants’ and interacting-others’ actor and partner effects create three between-clients clusters (normative, hyperactivating, deactivating), we will use an unsupervised machine learning algorithm, based on the k-means clustering method, developed by Hartigan and Wong [92].We chose the K-means clustering method because of its many advantages, including the fact that it is not model-based and applies optimization algorithms to define participants’ assignment to clusters [93, 94].We will implement the k-means clustering on the participants’ autoregressive and interactive effects and use the average silhouette method to determine the optimal number of clusters that best fit the data [95],computing the average silhouette of observations for different values of k. We will choose the number of clusters, k, as the one that maximizes the average silhouette over a range of possible values for k. We will use the R function *kmeans* in the *stat* package for clustering.

We will characterize the clusters found and identify the features that best differentiate between them in two steps: (a) compare the clusters on demographic and clinical characteristics (using ANOVA) and (b) build a classification tree using the *party* R package to predict cluster membership. We will explore whether the above measures of the intrapersonal and interpersonal characteristics of the individual are associated with the synchrony signature, determining whether the individual-specific signature is associated with constructs related to needs for closeness/dependence vs. autonomy. To achieve this, we will conduct a *machine learning classification tree analysis,* using random forest variable selection and Monte Carlo simulation for multiple testing adjustments [96]. To assess the robustness and consistency of the clustering, we will cross-validate the procedure described above using the validation set approach. In this method, the dataset is divided randomly into training and validation sets. The number of clusters is determined by the silhouette. Next, we will identify the determined number of k-means clusters for each training sample, and build classification trees for that number of clusters. The training sample is based on *P* = 20%, 30%, …, 90% of all clients. We will use the data of the other clients (P—100%) as a validation sample to classify them into the new clusters based on the newly created classification tree. We have successfully conducted these procedures in previous projects [97]^.^

##### The association between individual differences in the signature and mental health

We will test whether individual differences in the signatures are associated with individual differences in mental health. We will use ANOVA to explore whether the clusters identified differ in levels of mental health (symptom reduction, mental health) to test our hypothesis that the normative pattern will be associated with better mental health than either the deactivation or the hyperactivation pattern.

#### Power analysis

The main analyses will focus on the main outcome measure (HRSD [46]) and mapping the individual-specific signature and the association with mental health.

The sample size for Study 1 was chosen to provide adequate power to test our hypotheses. To determine the required sample size, we simulated data based on 1568 variables (784 combinations of the 28 features × 2, for the autoregressive + interactive features) for 60 participants with 6 repeated measurements, assuming a normal distribution with a variance of 1 for each variable, using cross-validation with 6 folds. In each fold, one measurement of each participant was removed and the classifier was used to classify the removed observation. In 1000 simulations, we obtained 83% correct classification.

##### Identifying individual differences in the activation of the synchrony system

Based on the power calculations and equations provided by Dalmaijer et al., [98] ‏we expect around 35–45 features to emerge in the support vector machine (SVM) (within- and between-modalities, both autoregressive and interactive features). We expect to find three equally sized subgroups. Between these subgroups, we expect large size differences (the first features in the SVM; Cohen’s d = 0.8) in 15–20, and medium size differences (the next features in the SVM; Cohen’s d = 0.5) in 20–25 features. Thus, based on the equation, the total expected separation is Δ = 3.8–4.3 and a power of 80% is expected for *N* = 60. Given attrition and missing data, we will sample 68 individuals: half non-depressed individuals and half with depression.

## Study 2

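### The 80% power stated for finding three synchrony types at N = 60 does not describe the planned k-means and silhouette rule, which picks three clusters in only about 51–76% of simulated runs under favourable assumptions

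*Protocol article*

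**What the plan says.** The Study 1 power section on individual differences in activation of the synchrony system expects 35 to 45 features to come out of the support vector machine. It assumes "large size differences (the first features in the SVM; Cohen’s d = 0.8) in 15–20" of them and "medium size differences (the next features in the SVM; Cohen’s d = 0.5) in 20–25 features". It adds: "We expect to find three equally sized subgroups". From equations in a cited source it concludes that "the total expected separation is Δ = 3.8–4.3 and a power of 80% is expected" at N = 60, and then: "Given attrition and missing data, we will sample 68 individuals".

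The analysis section on individual differences in the signature says how the clusters will be found. K-means is run on the selected autoregressive and interactive effects, and k is taken "as the one that maximizes the average silhouette over a range of possible values for k". The range of k is not given and no dimension-reduction step is named. The same section states: "We will use the autoregressive (actor) effect to estimate the deactivation pattern and the interactive (partner) effect to estimate the hyperactivation pattern".

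**The concern.** A power figure is useful only if it refers to the decision rule that will be applied. Here the 80% is tied to a total separation. The finding of three types will instead be decided by whether the average silhouette peaks at k = 3 on 35 to 45 separate features. Nothing in the article links the two.

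The separation also carries two unstated assumptions: that the features are independent, and that every pair of types is separated by the full amount. The first is doubtful, because all effects are pairings of the same 28 signals. The second is not obvious when actor effects are tied to one type and partner effects to another.

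The three-type hypothesis is central to Study 1, and the planned ANOVA compares the normative pattern with the other two. If the rule often returns two clusters when three types exist, that comparison cannot be made as planned. A two-cluster result could then be mistaken for evidence against the theory.

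**Working it through.** **Inputs from the article.** 15–20 features at d = 0.8; 20–25 features at d = 0.5; three equal groups, so 20 each at N = 60; k at maximum average silhouette.

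**Assumed, because not given.** Unit-variance normal features; feature correlation r of 0, 0.1 or 0.3; the layout of the three types; k searched from 2 to 6 or 2 to 8 (2 to 3 also tried); 10–25 random starts unless stated.

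**Step 1: reproduce the separation.** Δ = √(Σd²).
- 15 + 20 features: √(15 × 0.64 + 20 × 0.25) = √14.60 = 3.82
- 20 + 25 features: √(20 × 0.64 + 25 × 0.25) = √19.05 = 4.36

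This matches the stated 3.8–4.3 apart from trivial rounding at the upper end.

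**Step 2: what Δ assumes.** Three group means on one feature cannot all lie exactly d apart, so the full Δ for every pair is a generous case. Alternatives:
- Each feature separates one type from the other two, so each pair differs on two thirds of the features: √(14.60 × 2/3) = 3.12 and √(19.05 × 2/3) = 3.56.
- Actor features mark only deactivation and partner features only hyperactivation, so the normative type differs from each on half: √(14.60/2) = 2.70 and √(19.05/2) = 3.09.
- Normative midway between the other two: 3.82/2 = 1.91 and 4.36/2 = 2.18.

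With equal correlation r among p features and all effects in one direction, Δ² = [Σd² − r(Σd)²/(1 + (p − 1)r)]/(1 − r). At r = 0.1:
- p = 35, Σd = 22: [14.60 − 48.4/4.4]/0.9 = 4.00, so Δ = 2.00
- p = 45, Σd = 28.5: [19.05 − 81.225/5.4]/0.9 = 4.45, so Δ = 2.11

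**Step 3: simulate the stated rule.** Power here is the share of runs in which k = 3 is chosen. Ranges pool separate simulations.

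| Assumed structure, N = 60 unless stated | 15 + 20 | 20 + 25 |
|---|---|---|
| Independent, every pair at full Δ | 51–57% | 68–76% |
| Same, features standardised | 48% | 62% |
| Same, a single random start | 43% | 42% |
| Same, N = 66 | 63% | 78% |
| Independent, each feature separates one type from the other two | 21% | 23% |
| Independent, actor marks only deactivation, partner only hyperactivation | 3–5% | 2–3% |
| Independent, normative midway, extremes d apart | 1% | 0% |
| Every pair at full Δ, r = 0.3 | 0% | 0% |

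With every pair at full Δ and r = 0.1, results lay between 6% and 38% over both feature counts, depending on how the effects align with the correlation. For the first row, the largest simulation (600 runs per cell) gave 55.0% and 76.3%, with standard errors of 2.0 and 1.7 percentage points.

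**Step 4: why the first row is below 80%.** Noise in 35 to 45 unreduced dimensions flattens the silhouette (mean about 0.07), and k = 2 often wins. Projecting the ideal case to two principal components lifts the silhouette at k = 3 to 0.47–0.52 and the choice of k = 3 to 95–100%. The article states no such step. With it and r = 0.1, k = 3 was chosen in 50% and 48% of runs.

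**The case against.** The 80% is taken from a cited source whose power criterion is not available here, and it may define power differently from selection of k = 3. A journal article may also leave the range of k, the number of starts and any dimension reduction to a fuller plan. This stands to the extent that nobody can say from the article that the 80% was wrongly derived from its source. It does not rescue the figure as a description of the stated rule. If a reduction step is intended, the power depends on it, and the article should name it.

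A reader might infer that the plan's own definitions put power at 2–5%. The documents do not support that. They say which effect estimates which pattern. They do not say that hyperactivating participants share the normative actor mean, or that deactivating participants share the normative partner mean. That layout is suggested, not fixed.

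A reader might also blame the shortfall wholly on correlation and partial separation. It is already there when both are assumed away. Nor does correlation act in one direction only. With alternating effect signs, r = 0.1 raises Δ to √(14.60/0.9) = 4.03, and in the split layout it raised selection of k = 3 from 3–5% to 11–12%.

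Finally, the clustering is worded as exploratory, and N = 60 has a second basis in the 83% correct classification from the support vector machine simulation. The Study 2 interaction uses the trait-like signature, not membership of three clusters, so loss of that analysis does not follow. These points limit the consequences but do not make the 80% correct.

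**Conclusion.** The point holds. The stated 80% does not describe the rule that the article sets out. On the article's own effect sizes, with independent features and every pair fully separated, that rule selects three clusters at N = 60 in about 51–57% of runs with 35 features and 68–76% with 45. No scenario run on the unreduced features at N = 60 reached 80%.

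This rests on reading the rule as written, without dimension reduction, and on counting selection of k = 3 as success. The lower figures for correlated features and for features that mark one type are conditional on assumed values. They show how sensitive the power is; they do not estimate it. The arithmetic behind the separation is sound. The error is in attaching 80% to this rule.

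**What to change.** Replace the 80% with the simulated probability of selecting three clusters under the actual pipeline. State the layout of the three types, a range of feature correlations, the range of k, the number of starts and any dimension reduction. Restate the power for the planned N; no change in sample size is needed. Add that selection of k = 2 is not to be read as evidence against three types.

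Optionally, reduce dimension before clustering, for example to the mean standardised actor effect and the mean standardised partner effect. In the independent split layout this raised selection of k = 3 from 2–5% to about 58–79%. That is still below 80%, and it falls to about 40% at r = 0.1 (37% and 41%) and to 3–5% at r = 0.3. It improves power but does not restore the stated figure.

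The cost is one simulation and one restated figure, with no extra participants, and the article reports that recruitment had not begun. The stated power will be less favourable. Composites lose some feature-level detail, which can be reported descriptively.

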### Design

Study 2 investigates how deterministic the trait-like synchrony signature (as mapped in study 1) is in the absence of intervention, and whether changes in the signature are associated with changes in mental health as a result of intervention. The target relationships will be those with the therapist. All participants in Study 2 will have undergone the process described in Study 1 before starting their participation in Study 2. First, participants will be enrolled in a first session with a therapist. Second, participants will be allocated to a randomized control trial (RCT) and randomized to either a 16 weeks waiting list or supportive-expressive treatment (SET [99, 100]) with the therapist they met at the first session. To ensure balance across age, sex, family status, baseline 17-item HRSD [46], and personality disorders, a minimization algorithm will be used. At the end of treatment, the participants will again undertake the SIP [45]) vis-a-vis the same figures they interacted with before the therapy. At the end of the trial, participants who were randomized to the waiting list will be enrolled in treatment. The trial will follow the Standard Protocol Items: Recommendations for Interventional Trials (SPIRIT) checklist [101] requirements for an RCT [101] with a design that includes both treatment and waiting list conditions.

### Participants

Participants will be 78 patients diagnosed with MDD. Recruitment will take place through advertisements, offering free treatment at the University of Haifa Psychotherapy Research Lab clinic (Fig. 3). All participants will have previously enrolled in Study 1. The sample size was chosen to provide adequate power to test our hypotheses.

**Fig. 3 Fig3:**
[figure not shown]
Study 2 Flowchart

#### Inclusion criteria

(a) current MDD based on the MINI (Structured Clinical Interview for DSM5 [47, 48], and scores above 14 on the 17-item HRSD [46] at two consecutive assessments, one week apart; (b) for participants using psychiatric medication, the dosage must be stable for at least three months before the beginning of the study, and they will be asked to maintain stable dosage during the treatment; (c) age between 18 and 65 years [102]; (d) Hebrew language proficiency; (e) provision of written informed consent.

